## Abstract

**Background:**

Excessive earwax causes unwanted symptoms such as hearing loss, tinnitus, discomfort and changes in the quality of one’s own voice. The NHS Audiology Wax Removal Service in North Wales recommends the use of olive oil as a pretreatment wax softener administered as either drops or spray prior to microsuction. For one in four patients microsuction is unsuccessful at the first attempt. Anecdotal evidence suggests that the administration of olive oil as a spray is a more effective pretreatment. This trial aims to explore whether administering olive oil pretreatment softener is more effective when administered as drops or spray.

**Methods:**

This two-arm cluster randomised control trial will be conducted within the existing NHS Audiology wax removal service in North Wales from January to July 2025. This pragmatic trial involves 26 NHS GP practices (clusters) and compares the administration methods of olive oil pretreatment via drops and spray. A sample size of 1,742 participants (67 in each of the 26 practices) was calculated as sufficient to determine a clinically significant difference. Presumed consent is used for all eligible patients seen within the wax removal service. Patients will be advised to source and self-administer three drops or sprays of olive oil for seven days before attending a wax removal microsuction appointment with an audiology practitioner where routine anonymized data will be collected. The primary outcome is whether wax removal is successful, as assessed via visual examination. The secondary outcomes include: improvements in self-reported symptoms, the amount of residual wax following microsuction and the number of adverse events. Statistical analyses will be conducted with an intention-to-treat design to compare outcomes between the groups.

**Discussion:**

This RCT aims to investigate whether administering olive oil as a pretreatment wax softener via drops or spray affects the outcome of wax removal. The outcome of this trial will inform future recommendations to patients and improve service effectiveness and efficiency by reducing the need for repeat visits. The results will be shared nationally and used to inform national guidance on wax removal.

**Trial registration:**

ISRCTN, ISRCTN28211073. Registered 23 December 2024, https://www.isrctn.com/ISRCTN28211073?q=earwax&filters=&sort=&offset=1&totalResults=3&page=1&pageSize=10.

**Supplementary Information:**

The online version contains supplementary material available at 10.1186/s13063-025-09378-5.

## Introduction

### Background and rationale {6a}

Earwax is a naturally occurring substance that is produced within the ear and forms part of the ear’s self-cleaning and protective mechanism. It achieves this by trapping dust and dirt and removing them from the ear canal, resulting in antibacterial and antifungal properties [1–6]. Earwax usually migrates out of the ear canal via natural jaw actions, such as chewing and talking, but in some cases, it can accumulate excessively, leading to occlusion within the external ear canal. This causes various unwanted symptoms, the most common being hearing loss, with other self-reported symptoms such as tinnitus, a blocked ear, changes in the quality of one’s own voice, pain or discomfort, coughing, irritation, infections and even dizziness [1, 3, 5, 7–16]. Munro et al. [16] reported that the most common symptom of earwax was hearing loss (86.4% of patients), which affects daily living, including listening to TV and environmental awareness. Occluding earwax can also have a negative effect on a person’s quality of life by causing social withdrawal, reduced function at work, mild paranoia and disorientation [1, 11, 14].

The prevalence of problematic earwax is reported to be approximately 2.3 million people per year, or 5% of the general adult population, which is as high as 65% of the elderly population [1, 11]. Occluding wax will only clear spontaneously in 5% of cases, which explains why earwax removal, which is the most common ENT procedure undertaken in primary care, is performed on 4 million ears per year in the UK with the goal of resolving or reducing these unwanted symptoms [1, 12, 17].

#### Rationale

Despite earwax removal being a relatively common procedure, there is limited high-quality evidence on the most effective removal method. Many studies recommend the use of a wax softener prior to mechanical removal [18]. Wax softeners have been used for many years in all healthcare settings for the management of wax as a pretreatment prior to mechanical removal [2, 18–20]. There are various pretreatment wax softeners available, and studies have shown no difference in the use of olive oil, water or any other wax softener [1, 13, 19–21]. Using a wax softener alone may lead to complete clearance of the wax in approximately 20–22% of cases, but most often, it needs to be combined with mechanical removal [13, 19, 22, 23].

The NHS Audiology Primary Care service in North Wales offers a wax removal service located at GP practices. This is a needs-based pathway in which patients reporting symptoms consistent with excessive earwax can self-refer, or patients can be referred by professionals who confirm the presence of earwax that restricts a full view of the tympanic membrane for earwax removal. All patients are advised to use olive oil drops or spray as a pretreatment wax softener followed by attempted earwax removal via microsuction by audiology practitioners as a first-line treatment. The service evaluation data revealed that one in four patients required a return visit for a second attempt at wax removal, with the first attempt being unsuccessful due to incomplete removal of wax, as reported by the audiology practitioner. Anecdotal evidence from our practitioners suggests that administering olive oil as a spray may lead to an improved success of wax removal compared with the traditional method of administering drops. This may be due to more effective coverage and contact with the wax, which is in agreement with Oron et al. [24], who reported that spray may penetrate deeper into the ear canal during application.

This large-scale cluster randomised control trial aims to compare the administration methods of olive oil drops and olive oil spray as a pretreatment wax softener prior to wax removal by microsuction. No previous study has investigated whether the application of wax softeners via different methods affects the outcome of wax removal. The trial has full support from a public and patient involvement (PPI) group who have been consulted throughout the trial design and who will also be involved in the analysis and dissemination of results. PPI individuals reported this research to be valuable and important, especially within the theme and focus on preventative care and care in the community.

### Objectives {7}

Primary objective: To compare the success of wax removal following the use of olive oil pretreatment with wax softener intervention (spray) and comparator (drops) for 7 days prior to microsuction. The success of wax removal is determined by complete clearance of wax not requiring a second visit to the clinic, as reported by the audiology practitioner upon otoscopic examination following microsuction.

Secondary objectives:

The secondary objective outcomes will be compared between the olive oil drops and olive oil spray groups.To explore improvements in self-reported symptoms following wax removal, a self-reported improvement scale is used.To investigate the postmicrosuction visualisation ratings (a measure of the amount of residual wax).The occurrence of adverse events associated with microsuction are monitored according to Clegg et al. [25].

### Trial design {8}

This RCT is a parallel, two-arm, superiority cluster randomisation trial design to compare the effectiveness of olive oil drops and olive oil spray when used as a pretreatment wax softener prior to wax removal by microsuction. A cluster randomised design was chosen to ease the organisation of the trial, as it takes place within a current clinical service, and individual randomisation would add to the workload and make the trial difficult to undertake. Twenty-six GP practices will be included and randomised via a one-to-one allocation ratio to either the intervention arm (olive oil spray) or the comparator arm (olive oil drops) prior to the start of the study. The trial is designed to have a pragmatic approach, with the data analysed via an intention-to-treat analysis. Figure 1 presents the trial flow chart. Minimal changes are introduced to the service as part of this trial but include:Verification of one of the secondary outcomes, which involves reporting the amount of residual wax following microsuction by the audiology practitioner. The amount of residual wax following microsuction is recorded by the audiology practitioner via a visual verification rating (0–3); see Table 1. A video otoscopy image will be taken with patient consent and sent to an independent professional, who will rate the amount of residual wax using the verification ratings. The ratings of the audiology practitioner and independent professional will be compared to verify the reliability of this outcome.Patients will be given a feedback slip at the end of the appointment with the audiology practitioner and asked to select which pretreatment wax softener they used. This information will be used to check adherence to the protocol when analysing the outcomes given that the pretreatment wax softener is purchased and self-administered by the patient.

**Fig. 1 Fig1:**
[figure not shown]
RCT flowchart

**Table 1 Tab1:** Descriptors for visualisation ratings used postmicrosuction by audiology practitioners

Visualisation rating	Explanation
0	No or very minimal earwax, complete visualisation of tympanic membrane
1	Minor amount of earwax with majority of tympanic membrane visible
2	Moderate amount of earwax with only part of the tympanic membrane visible
3	Fully occluding wax, no visualisation of tympanic membrane

## Methods: participants, interventions and outcomes

### Study setting {9}

The study will run within 26 NHS-funded GP practices that deliver the NHS Audiology Primary Care wax removal service across North Wales. The earwax removal service is delivered by audiology practitioners. Patients with symptoms, or a clinical need, can self-refer, be referred by their audiology practitioner, GP or other healthcare professional working in the practice. The research will not change service provision or routine clinical care for research participants or other patients seen within the service during the research timeline.

### Eligibility criteria {10}

All adults over 18 years of age with the presence of earwax in one or both ears are eligible for the study.

Inclusion criteria:Adults over 18 years of ageProvide informed consent for microsuctionPresence of wax given rise to symptoms or need that warrants removal

The exclusion criteria include:Under 18 years of ageActive ear infectionActive dermatitisPerforated or nonintact tympanic membraneForeign bodies present in the ear canalAny contraindication for microsuction or use of wax softeners – previous ear surgery including mastoid obliteration; grommets in situ

### Who will provide informed consent? {26a}

Consent to participate in this trial will be presumed, as the study participants in both arms are NHS patients accessing standard NHS care, and this approach has been approved by ethics. The only difference between the two arms is that patients will be advised to use either pretreatment olive oil drops or spray rather than having a free choice of using either solution.

Written consent will be obtained from a selection of patients as part of the verification of visualisation ratings for outcome verification (see Fig. 1). Five patients seen by 90% of the audiology practitioners will be asked to provide consent for a video otoscopy image of their external ear canal. The CI will obtain informed consent and take video otoscope images. This image will be shared with an independent professional for outcome verification purposes. A copy of these signed and dated forms will be kept in the patient’s audiology records, and another file with trial documentation will be included in the research file. These will not be shared with anyone outside the research team.

### Additional consent provisions for the collection and use of participant data and biological specimens {26b}

Not applicable – There are no additional consent provisions for sharing data with others in this trial.

## Interventions

### Explanation for the choice of comparators {6b}

The comparator in this trial is olive oil drops, which are traditionally the most commonly used pretreatment wax softener within our wax removal service. The olive oil will be self-administered at home by the patient or a significant other at a recommended dose of 3 drops per ear once a day for 7 days prior to the wax removal appointment. Following feedback from the PPI individuals, advice was given by a Trial Pharmacist, who confirmed that olive oil sold for wax removal purposes in pharmacies has been through medical-grade testing rather than ordinary kitchen olive oil, so this is recommended for use as part of this trial.

### Intervention description {11a}

The intervention in this trial is olive oil spray. Patients will be advised to use the allocated olive oil solution when booking their wax removal appointment at the GP practice. The olive oil will be self-administered at home by the patient, or a significant other, at a recommended dose of 3 sprays per ear once a day for 7 days prior to the wax removal appointment. Notably, olive oil spray has a greater cost than does the comparator. This was discussed with the PPI individuals, who deemed the price difference acceptable and unlikely to influence many participants.

### Criteria for discontinuing or modifying allocated interventions {11b}

All patients will be encouraged to follow the pretreatment advice as part of this trial. The option to discontinue or modify the pretreatment advice will be at the discretion of the healthcare practitioner should this be clinically indicated.

### Strategies to improve adherence to interventions {11c}

Patient information leaflets are available at participating GP practices that specifically instruct patients to administer pretreatment olive oil as per the allocation of the GP practice. The patient information leaflet highlights that the research is being carried out to investigate any differences between these two administration methods, hence the importance of adhering to the intervention.

Staff reminder slips will be issued to GP practices to be placed in reception and administration offices. Additionally, staff members will be reminded regularly of the importance of encouraging patients to use the allocated solution both by the research team and the Audiology Primary Care team.

Following PPI feedback regarding the occasional lack of stock of olive oil spray in community pharmacies, local community pharmacy networks have been informed of the research to encourage local pharmacies to keep stock of both drops and sprays for patients to purchase locally.

### Relevant concomitant care permitted or prohibited during the trial {11d}

Patients may be offered concomitant care for hearing or balance assessment alongside this trial if needed.

Patients will be given verbal pre-appointment instructions when booking their wax removal appointment to use the olive oil drops or spray solution. They will be advised to use three drops or sprays of the olive oil, once a day for seven days prior to their wax removal appointment. Written information will be available for those that arrange their wax removal appointment whilst in the GP practice. The patient information leaflet specifies to use olive oil drops or spray only (depending on cluster allocation) and not any other available wax softener. These instructions will be given verbally to those patients who arrange their wax removal appointment by phone.

### Provisions for posttrial care {30}

Not applicable to this trial, as patients will only remain in the trial for the duration of one clinical visit, and there are no other deviations from normal clinical care.

### Outcomes {12}

#### Primary outcome

The primary outcome is a comparison of the success of wax removal across the two groups. Success of wax removal is measured by the Audiology Practitioner, who inspects the ear and calculates the proportion of patients where wax removal is successful (0 or 1 as defined in Table 1) at the first attempt and who do not need a repeat visit (2 or 3 as defined in Table 1).

#### Secondary outcomes

The secondary outcomes include the following:Improvements in self-reported presenting symptoms (reported by patients during clinic visits prior to microsuction) measured via a 5-point improvement rating scale (much better, slightly better, about the same, slightly worse, and much worse) following wax removal in the two groups.Differences in the amount of residual wax following microsuction are measured by a postmicrosuction visualisation rating reported by the audiology practitioner through visual inspection of the ear. See Table 1.Adverse events. All adverse events that occur in the clinic during or immediately after microsuction and any reported by patients up to one week after microsuction, will be recorded as per normal clinical practice.

A further exploratory analysis will be completed on the following:The effect of age on the success of wax removal.Success of wax removal in patients who do not use any pretreatment.

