### Adverse event reporting and harms {22}

Adverse events are not anticipated during this trial, as the two interventions are routinely used. Unexpected severe adverse events (SAEs) associated with the standard care intervention (ear wax removal) will be reported to the sponsor as per our Standard Operating Procedure for Safety Reporting and further assessed by the CI in addition to following standard clinical care procedures. Non-severe adverse events will be recorded, assessed, reported and managed as per normal service delivery and departmental policy and as stated in the research protocol.

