## Abbreviations

AE: Adverse event
BCUHB: Betsi Cadwaladr University Health Board
CI: Chief investigator
ENT: Ear, nose and throat
GCP: Good clinical practice
GP: General practice
HCRW: Health Care Research Wales
NHS: National Health Service
PPI: Patient and public involvement
REC: Research Ethics Committee
R&D: Research and development
SAE: Serious adverse event

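### The adverse-event outcome is tied to microsuction, while the randomised difference is the softener used at home beforehand, so direct softener reactions are not systematically collected

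*Protocol article*

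**What the plan says.** All references are to the protocol article.

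- **Objectives {7}:** the harm objective reads "The occurrence of adverse events associated with microsuction are monitored". The secondary outcomes are to be compared between the two softener groups.
- **Outcomes {12}, Secondary outcomes:** the events to be recorded are "All adverse events that occur in the clinic during or immediately after microsuction and any reported by patients up to one week after microsuction".
- **Adverse event reporting and harms {22}:** "Adverse events are not anticipated during this trial, as the two interventions are routinely used". On escalation: "Unexpected severe adverse events (SAEs) associated with the standard care intervention (ear wax removal) will be reported to the sponsor". On the rest: "Non-severe adverse events will be recorded, assessed, reported and managed as per normal service delivery and departmental policy", with a further reference to the research protocol.
- **Abbreviations:** "SAE: Serious adverse event".
- **Statistical methods {20a}:** adverse events in the two groups are summarised descriptively.

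The sections on consent {26a}, comparators {6b} and intervention {11a} establish that the arms differ only in drops or spray, which patients apply themselves at home over the 7 days before the appointment.

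**The concern.** A harm comparison between randomised arms should cover the time when the arms are treated differently. Here that is the week of oil before the visit. The three places that define harms point instead to the procedure that both arms receive, and to the week after it.

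What is at stake is how the adverse-event table will be read. Under Dissemination plans {31a}, the trial may change advice to patients across Wales and is to be shared with national guidance bodies. A table with similar counts in the two arms could be taken as evidence that the products are equally well tolerated. It would not show that if reactions at home were never asked about. The protocol itself allows that softeners may not suit everyone: Eligibility criteria {10} exclude patients with a contraindication to them, and section {11b} lets a practitioner stop or change the pretreatment advice on clinical grounds.

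**Working it through.** **Timing.** Call the appointment day 0. The allocated oil is used over the 7 days before it. The outcome definition has two limbs. The first dates an event by when it occurs: in the clinic, on day 0. The second dates it by when the patient reports it: up to day +7. The first limb covers 0 of the 7 home-exposure days. The second says nothing about when the event began.

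**Four kinds of event against the text.**

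| Event | Outcome definition | Objective | Result |
|---|---|---|---|
| Reaction to the oil before the visit, not mentioned | Neither limb | Not linked to microsuction | Not counted |
| Reaction to the oil before the visit, volunteered at the visit or in the week after | Fits the reporting limb | Not linked to microsuction | Unclear |
| Oil makes microsuction harder or more painful | Fits | Linked | Counted; can differ by arm |
| Event due to microsuction alone | Fits | Linked | Counted; no difference by arm expected |

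**Is anyone asked?** Section {18a} lists the data. Before microsuction: date, location, age, referral source and presenting symptoms. After it: residual wax and symptom improvement. The slip in Trial design {8} asks which softener was used. None of these asks about a reaction to the oil. Presenting symptoms do not fill the gap, because Background {6a} lists pain, irritation and dizziness as symptoms of wax itself. A reaction entered there could not be told apart from the reason for attending.

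**Route for late reports.** The outcome accepts reports for a week after the visit, but section {18a} says that all data are recorded at one visit, and section {30} keeps patients in the trial for that visit only. These statements must be reconciled.

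**Scale.** The planned total is 26 × 67 = 1,742, or 1,742 / 2 = 871 per arm. It reproduces from the stated inputs: design effect 1 + ((1 + 0.527²) × 67 − 1) × 0.02 = 2.692, giving 80.0% power for 0.74 against 0.83 (normal approximation, unpooled variance, two-sided 5% assumed). It serves here only as the denominator. The documents give no softener reaction rate. Expected reactions per arm at assumed rates:

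- 0.5%: 0.005 × 871 = 4.4
- 1%: 0.01 × 871 = 8.7
- 2%: 0.02 × 871 = 17.4
- 5%: 0.05 × 871 = 43.6

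The share of these that patients would volunteer, and that practitioners would then record, is unknown.

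**The case against.** **The outcome is not empty.** A reader might infer that the harm outcome can detect no harm of either product and would count no softener reaction. The documents do not support that. The reporting limb restricts when an event is reported, not when it started, so a volunteered reaction could be counted. Randomised pretreatment also precedes microsuction and can change how difficult or uncomfortable it is. An effect of the oil that persists to the visit would fall within the window too. This stands, and it limits the point to direct reactions before the visit that nobody asks about.

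**Details may be elsewhere.** Non-severe events are left partly to departmental policy and to the full research protocol, which is not shown. Their detailed handling cannot be assumed absent. The article does, however, print the objective and the outcome definition, and a handling rule does not by itself widen them.

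**It is a deliberate pragmatic choice.** Both products are in routine use, patients with contraindications are excluded, data collection is confined to routine items, and a change in recommendations is tied to effectiveness. This is fair, and it lowers the priority. It does not make a microsuction-based count a comparison of how well the products are tolerated.

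**The added data would be noisy.** Patients know their allocation, and wax symptoms resemble reactions. This stands as a cost of the fix.

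**Severe and serious.** A reader might infer that an event that is serious but not severe would miss sponsor reporting. That goes beyond the text, because section {22} refers to a sponsor operating procedure that is not shown. What stands is that the term and its abbreviation do not match.

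**Conclusion.** The concern holds in limited form. The objective, the outcome and the sponsor-reporting rule are tied to microsuction or wax removal, and no listed item asks about the 7 days in which the arms differ. Direct softener reactions before the visit are not systematically collected, and the status of volunteered ones is ambiguous. Effects that act through microsuction remain visible.

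The size of the gap is 0 of 7 home-exposure days under the in-clinic limb, with an unknown fraction recovered through volunteered reports. The event counts above rest on assumed rates and only indicate scale. The conclusion rests on the article's wording and would soften if the full protocol includes a prompted question about the softener week. It affects a descriptive secondary outcome and leaves the primary analysis untouched. The *severe*/*serious* mismatch is a separate, smaller wording point.

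**What to change.** 1. Define the adverse-event outcome to include events from first application of the allocated softener, and say that events volunteered at or after the visit count.
2. Add one fixed question to the existing patient slip: any new or worse ear symptom after starting the oil and before microsuction. Data management {19} describes practice slips with a clinic code related to allocation, so counts by arm are possible without identifying patients. That section also appears to have the code-to-allocation file deleted when data collection ends, so events must be assigned to arms before then.
3. Report by arm in two periods: pretreatment, and microsuction to one week.
4. Reconcile *severe* in section {22} with *Serious* in the Abbreviations, and state whether sponsor reporting covers events associated with the allocated softener.

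**Cost.** A protocol amendment with its approvals, some wax symptoms reported as reactions, and partial coverage. Trial status gives collection from 1 January to 31 December 2025 and a version date of 26 August 2025 (day 238). At best (365 − 238) / 365 = 35% of the period would remain, or about 0.348 × 871 = 303 patients per arm if accrual is even. The Abstract gives January to July 2025, under which none would remain.

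**If the question cannot be added,** label the outcome as microsuction-period adverse events and draw no conclusion on the comparative safety of the two products. That costs only wording.
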